***Primary analysis***

**Pharmacokinetic analysis**

The following pharmacokinetic parameters will be calculated using standard two-stage approach involving calculation of pharmacokinetic parameters in those patients in whom a full PK curve was recorded:

1. C
_max_ - the peak concentration of the drug after administration2. T
_max_ - the time to reach C
_max_
3. AUC
_0-24_ - area under the time concentration curve from hour 0 to hour 244. Time > MIC is the duration of time where the drug concentration level is greater than the minimal inhibitory concentration for the
*M. tuberculosis* isolate (either the individual or the median MIC of the study population)

**Safety analysis**

The number and proportion of individuals who reported any kind of clinical grade 3-5 AE during the study period will be presented by intervention arm. Data for safety will be analysed in accordance with the ITT principle. The main analysis will be a composite safety endpoint over the 8-week intervention period:

AEs, clinical Grade 3-5 as classified by DAIDS Toxicity ScaleAll SAEsDILI, grade 3-5 (ALT >3x ULN with symptoms or 5x ULN without symptoms)Discontinuation of rifampicin for >5 days in the first 8 weeks for any cause

Time to experiencing an adverse event will be compared between treatment arms using cumulative incidence functions and a Cox proportional hazards regression model adjusted for site and BMRC TBM grade. Death will be considered a competing risk. The individual subgroups of AEs that make up the composite endpoint will be summarised. A secondary analysis of rifampicin-related toxicity (probable or definitely related, as assigned on the adverse events case record form) will be presented by intervention arm.

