### Endpoints

***Primary end points***

*1. Pharmacokinetic parameters*

Plasma and CSF rifampicin area under the curve (AUC
_0-24h_), and maximum concentration (C
_max_)

*2. Adverse events*

We will use a composite safety endpoint for the 8-week intervention period that includes clinical grade 3-5 adverse events (AEs) (as classified by Division of AIDS (DAIDS) Toxicity Scale) or all serious adverse events (SAEs), drug-induced liver injury (DILI), grade 3-5 defined by alanine transaminase (ALT) >5x upper limit of normal (ULN), or discontinuation of rifampicin for >5 consecutive days in the first 8 weeks for any cause.

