### Adverse events and safety reporting

The principles of ICH GCP require that both investigators and sponsors follow specific procedures when notifying adverse events or reactions in clinical trials. The definitions of the EU Directive 2001/20/EC Article 2 based on the principles of ICH GCP apply to this trial protocol. All adverse events will be assessed for seriousness, causality and expectedness. Causality in relation to study drug (rifampicin) is assessed as unrelated, unlikely, possible, probable or definite based on temporal relationship and clinical judgement. If the event is serious and unrelated or unlikely to be related it is classified as an SAE. If the event is possibly, probably or definitely related it is classified as a Serious Adverse Reaction (SAR). Expectedness of the adverse reaction is assessed using the
summary of product characteristics (SPC) at the time of the event. An unexpected adverse reaction is one not previously reported in the SPC, or one that is more frequent or more severe than previously reported. If a SAR is assessed as being unexpected it becomes a suspected unexpected serious adverse reaction (SUSAR). Intensity will be graded using the DAIDS toxicity scale.

The Trial Management Group at the Infectious Diseases Institute (IDI) must be notified of all grade 3-5 AEs, SAEs and SARs within 24 hours, thereafter they are responsible for reporting SAEs, SUSARs to the Sponsor, regulatory authorities and ethics committees in accordance with local regulatory and institutional guidelines.

***Interim analyses.*** Interim analysis of safety will occur after 24 participants (8 per arm) have completed the week 8 visit. The committee can modify the frequency of interim analysis and early termination could occur if the data safety committee decides there is an unacceptable level of toxicity in any of the investigational arms.

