### Statistical considerations

***Sample size.*** Approximately 800 adults presenting with symptoms of meningitis will be assessed, of which it is anticipated two-thirds will have cryptococcal meningitis. The circa 240 patients with negative CSF cryptococcal antigen (crAg) will undergo a comprehensive TBM diagnostic panel (Xpert MTB/Rif, Xpert Ultra, mycobacterial growth indicator tube (MGIT) culture, and/or next generation sequencing) from which we anticipate 60 people with suspected or confirmed TBM will be recruited into the randomised trial.

The sample size is determined following the assumption that PK parameters are normally distributed on the log scale. Estimated rifampicin log-transformed C
_max_ standard deviation is taken from
*Ruslami et al*.
^1^ The global study significance level (alpha) will be 10%, which is appropriate for phase II studies. Using the Bonferonni correction for multiple testing, each individual comparison will be made with alpha of 5%. Group sample sizes of n=15 achieve 90% power to reject the null hypothesis of equal means when the log-transformed population mean difference is 0.54mg/L with standard deviation of ±0.36mg/L in the control group and ±0.48mg/L (33% higher) in the experimental group, with a significance level of 0.05 using a two-sided, two sample unequal variance t-test. If the standard deviation differs from our estimate, the overall detectable effect size at 90% power will be 1.5 times the standard deviation, and 1.27 times the standard deviation at 80% power. We will not formally compare equivalence of the two investigational arms as this would require a larger sample size. Comparison of the two investigational arms will be primarily descriptive.

This phase II study would be underpowered to detect a survival benefit unless the effect size is large. A one-sided log rank test with 20 subjects per arm provides 80% power at 0.05 significance to detect a hazard ratio of 0.285 when 40% of controls survive 8-weeks. This assumes no more than 1 person drops out or is lost to follow-up per arm. The prior lost to follow up rate has been <1% in recent Ugandan meningitis trials.

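### Death is a component of the primary 8-week safety composite, yet the analysis of that composite treats death as a competing risk

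*Protocol article*

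**What the plan says.** The composite appears in two places in the protocol article. Under Primary end points it joins clinical grade 3-5 adverse events "or all serious adverse events (SAEs"), grade 3-5 drug-induced liver injury and prolonged discontinuation of rifampicin. Under Safety analysis the list opens with "AEs, clinical Grade 3-5 as classified by DAIDS Toxicity" and again takes all SAEs. That section introduces the list with "The main analysis will be a composite safety endpoint over the 8-week intervention period".

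Directly after the list comes the method: "Time to experiencing an adverse event will be compared between treatment arms using cumulative incidence functions and a Cox proportional hazards regression model". Site and BMRC grade are the adjustment variables. The next sentence is "Death will be considered a competing risk". It makes no exception for fatal events. The Cox model is not identified as cause-specific or subdistribution. The individual components are only to be summarised.

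On seriousness, Adverse events and safety reporting states: "The definitions of the EU Directive 2001/20/EC Article 2 based on the principles of ICH GCP apply to this trial protocol". The same section classes a serious event that is unrelated, or unlikely to be related, to rifampicin as an SAE.

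**The concern.** A competing event is one that prevents the event of interest from occurring. Here death is itself an event of interest, as a grade 5 adverse event and as a serious event. A participant whose first qualifying event is death in week 2 is an event under the endpoint definition and a non-event under the competing-risk sentence.

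This concerns a primary endpoint in a disease with very high early mortality: the Abstract gives 44% in hospital, and the survival power statement takes 60% of controls as dead by 8 weeks. Deaths could therefore be a large part of the composite. If fewer patients die on high-dose rifampicin, counting death makes that arm look safer. Treating death as competing leaves more of its patients alive to have a non-fatal event, so its cumulative incidence rises. The trial is open-label, and the choice between the readings should not be made once data have accrued.

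**Working it through.** **Is death in the composite?** The article does not spell out that grade 5 is death or that death is serious. Both follow from the DAIDS scale and the ICH GCP/EU definitions it adopts. Limiting the composite to drug-related deaths is not available, because unrelated serious events are classed as SAEs and the composite takes all SAEs. A related fatal event is relabelled a serious adverse reaction but remains a grade 5 adverse event.

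**The plan's own figure.** The safety composite has no stated figure, so I checked the survival statement that supplies the mortality inputs: "A one-sided log rank test with 20 subjects per arm provides 80% power at 0.05 significance", for a hazard ratio of 0.285 with 40% of controls alive at 8 weeks.
- High-dose survival = 0.40^0.285 = 0.770, so deaths are 60% versus 23%.
- Expected deaths with 20 per arm = 20 × (0.600 + 0.230) = 16.6.
- One-sided Schoenfeld power = Φ(√(16.6/4) × |ln 0.285| − 1.645) = Φ(0.91) = 82%. Simulation gives 79.7%.

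The stated 80% reproduces.

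**Model for the two readings.** Assume constant hazards over the 8 weeks and independence. Let h be the cumulative hazard of a non-fatal qualifying event and m that of death without an earlier one.
- Death counted: 1 − exp(−(h + m)).
- Death competing: h/(h + m) × [1 − exp(−(h + m))].

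The article gives no non-fatal rate for this population. I assume 30% in both arms, that is, no difference in toxicity: h = −ln 0.70 = 0.357.

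**At the detectable effect.** Control m = −ln 0.40 = 0.916; high-dose m = 0.285 × 0.916 = 0.261.
- Death counted: control 1 − 0.70 × 0.40 = 72.0%; high dose 1 − 0.70 × 0.770 = 46.1%. Hazard ratio (0.357 + 0.261)/(0.357 + 0.916) = 0.49.
- Death competing: control 0.357/1.273 × 0.720 = 20.2%; high dose 0.357/0.618 × 0.461 = 26.6%. Cause-specific hazard ratio 0.357/0.357 = 1.00.

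In patients out of 20, that is 14.4 versus 9.2 and 4.0 versus 5.3.

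**Range over the mortality effect** (control versus high dose, 30% non-fatal risk in each arm):

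| Mortality inputs | Death counted | Death competing | Cause-specific HR |
|---|---|---|---|
| 60% v 23% (survival power statement) | 72.0% v 46.1% | 20.2% v 26.6% | 1.00 |
| 55% v 24% (earlier intravenous trial, 8 weeks) | 68.5% v 46.8% | 21.2% v 26.4% | 1.00 |
| 44% v 24% (Abstract's in-hospital figure for control; 24% as above) | 60.8% v 46.8% | 23.2% v 26.4% | 1.00 |
| 60% in control, HR 0.94 (large Vietnamese trial) | 72.0% v 70.4% | 20.2% v 20.6% | 1.00 |
| 44% v 44% | 60.8% v 60.8% | 23.2% v 23.2% | 1.00 |

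For the HR 0.94 row, high-dose m = 0.94 × 0.916 = 0.861. Then 1 − 0.70 × exp(−0.861) = 70.4%, and 0.357/1.218 × 0.704 = 20.6%.

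**Deaths that follow an earlier event.** These patients count identically under both readings. In the first row, cut m to a quarter (0.229 and 0.065). Death counted gives 1 − 0.70 × exp(−0.229) = 44.3% versus 1 − 0.70 × exp(−0.065) = 34.4%. Death competing gives 0.357/0.586 × 0.443 = 27.0% versus 0.357/0.422 × 0.344 = 29.1%. The competing-risk gap falls from 6.4 to 2.1 points.

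**The case against.** The strongest defence is that the endpoint definition governs. Every death is then already an event, no competing death remains, the cumulative incidence equals one minus Kaplan-Meier, and the sentence is merely redundant. That reading is possible, but nothing in the article says the definition prevails, and a sentence written to have an effect would have none. A second defence is that the sentence refers to single non-fatal event types, where a competing risk is proper, as it is for normalisation of GCS under Clinical outcomes. But it directly follows the composite named as the main analysis, without any such limit.

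Objections to the size carry more weight:
- A reader might infer that the safety hazard ratio itself reverses. With equal non-fatal hazards it does not: a Cox model censoring at death gives 1.00, and only the cumulative incidences change order. Opposite hazard ratios need a further assumption that non-fatal toxicity differs.
- A reader might infer that mortality is expected to differ by the amount used. The hazard ratio of 0.285 is a detectable effect, given to show that the trial is underpowered for survival unless the effect is large. Lower mortality is a secondary hypothesis, and the Introduction describes equipoise.
- A reader might infer that this sentence decides which dose goes to phase III. The Introduction and Discussion tie that choice mainly to pharmacokinetics and pharmacodynamics, with safety as a condition. Mortality, the composite's components and rifampicin-related toxicity are also reported separately, so an excess of deaths or toxicity would not be hidden.

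**Conclusion.** Wrong as written. The conflict between the definition and the analysis sentence does not depend on any numerical assumption: deaths without an earlier qualifying event are in the primary safety endpoint under one and out of it under the other.

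Its effect on results is conditional. An opposite ordering of the cumulative incidences requires a mortality difference between arms and enough deaths with no earlier qualifying event. The opposite ordering at the detectable effect is an illustration resting on an assumed 30% non-fatal risk, constant hazards and independence. At a mortality hazard ratio of 0.94 the competing-risk gap is 0.4 points, less than one patient in 20, and with equal mortality it is nil. The documents do not support saying that the trial's safety conclusion will reverse.

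**What to change.** 1. For the composite as defined, state that death within 8 weeks counts as an event, analyse time to first event by Kaplan-Meier and the adjusted Cox model, and delete the competing-risk sentence for this endpoint.
2. Keep death as a competing event only for a supportive analysis of the first non-fatal component (grade 3-4 adverse event, non-fatal serious event, drug-induced liver injury, discontinuation of rifampicin). Present cumulative incidence functions and state that the Cox model is cause-specific. Non-fatal toxicity is then read from this analysis, next to the mortality comparison already planned.

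The cost is two sentences and one supportive analysis. No extra data or participants are needed.

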**Clinical outcomes**

Survival at 8 and 24 weeks will be calculated using the risk difference, from a generalised linear regression model adjusted for site and BMRC TBM grade. Kaplan-Meier curves will also be used to compare time to death between treatment arms, with censoring and loss to follow-up handled as previously described. Cox proportion hazards regression will be used to assess the effects of rifampicin dose, plasma/CSF rifampicin concentration, HIV, MRC severity grade and baseline GCS on survival.

When calculating time to normalization of GCS continuous-valued secondary endpoints will be compared with general linear models or Wilcoxon rank-sum tests as appropriate. Death can be considered a competing risk. χ
^2^ test will be used for comparison of proportions of patients with TBM-IRIS by intervention arm.

***Secondary analysis.*** We will explore the relationship between rifampicin exposures and clinical outcomes using a population pharmacokinetic-pharmacodynamic model. We will consider C
_max_ and AUC
_0-24h_ as the exposure variables. Survival, proportion with normalisation of conscious level and functional status (as determined by modified Rankin score) are the response variables.

***Planned subgroup analyses.*** Specified high-risk subgroups are of interest because of potential different responses to intravenous rifampicin from both an efficacy and safety perspective, and the clinical utility in future physician decision-making. With standard therapy, worse clinical outcome is associated with altered mental status, high organism burden. Subgroups of interest include:

1. TBM Diagnostic category (Definite, Probable, Possible)
^33^
2. British Medical Research Council (BMRC) TBM disease severity
^7^
3. CSF inflammation (CSF white blood cells) by tertiles4. CD4 at study entry5. ART status at study entry

***Analysis of ancillary studies.*** The results of ancillary studies will be reported separately from the main trial.

Findings of the diagnostic sub-study will be reported in line with the Standards for the Reporting of Diagnostic Accuracy studies (STARD) guidelines. Sensitivity and specificity will be calculated against a composite reference standard (any positive CSF test for
*M. tuberculosis*) and against the published uniform case definition of ‘probable’ or ‘definite’ TBM
^33^. A latent class analysis will also be performed.

The studies on brain tissue concentration at autopsy will be primarily descriptive.

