***Secondary endpoints***

*1. Mortality*

Mortality at 8- and 24-weeks post randomisation will be compared between study arms.

*2. Time to normalization of conscious level*

We will determine days from randomisation until observation of a GCS of 15 which is achieved for ≥2 consecutive days.

*3. Functional status*

The modified Rankin scale at 8 and 24 weeks will be used in determining functional outcomes.

*4. TB immune reconstitution inflammatory syndrome*

TB-IRIS will be diagnosed according to published case definitions
^31^. TB-IRIS will be determined independently by 2 trial clinicians blinded to treatment allocation.

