### Ethical considerations

***Confidentiality.*** Participants will be identified only by means of a coded identification number specific to each participant. All participant-related information (including CRFs, laboratory results, radiology reports etc.) will be kept strictly confidential. All records will be kept in a secure, locked location and only research staff will have access to the records. With consent, information relevant for the future HIV care will be shared with relevant HIV clinic for continuity of care and patient safety.

All computerized databases will identify participants by numeric codes only, and will be password-protected. Upon request, participant records will be made available to the study sponsor, monitors, applicable regulatory entities, including the Uganda National Council of Science and Technology, Uganda National Drug Authority, Mulago Institutional Review Board, or London School of Hygiene and Tropical Medicine.

***Consent.*** An estimated >80% of the study population will have altered mental status at initial hospital presentation. Those presenting with meningitis and altered mental status are at the greatest risk of death, and enhanced TBM therapy may have the greatest benefit for them. This hypothesis deserves testing via inclusion into the clinical trial. Secondly, as most persons with TBM present with altered mental status, in order to make results generalizable to all TBM patients, we wish to offer enrolment to all persons. Subjects unable to give informed consent due to altered mental status may have surrogate consent provided by proxy from their caregiver/next of kin.

For subjects enrolled by surrogate consent, if and when the participant regains the physical and mental capacity to give consent, information will be provided to them and written informed consent will be sought for continuation in the trial. If a patient or representative declines to give consent for continuation at this stage, his/her wishes will be respected.

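### Time to GCS normalisation: the named tests (linear model or rank-sum) do not, as stated, treat death as a competing event, so a comparison of observed times can mislead

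*Protocol article*

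**What the plan says.** All places are in the protocol article.

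- **Secondary endpoints** defines the outcome: "We will determine days from randomisation until observation of a GCS of 15 which is achieved for ≥2 consecutive days". It gives no value to a participant who dies first or never reaches that state.
- **Statistical considerations, Clinical outcomes** names the tests: "When calculating time to normalization of GCS continuous-valued secondary endpoints will be compared with general linear models or Wilcoxon rank-sum tests as appropriate". The next sentence reads: "Death can be considered a competing risk". It names no estimator or test for that purpose.
- **Safety analysis** is firmer about the adverse-event endpoint: "Time to experiencing an adverse event will be compared between treatment arms using cumulative incidence functions". There a Cox model is also named, and death is to be a competing risk without any *can*.
- **Statistical methods** says that all analyses are adjusted for site and BMRC grade.
- **Sample size** gives the assumption about death in its survival power statement, which sets control survival with the words "when 40% of controls survive 8-weeks" and takes a hazard ratio of 0.285 with 20 participants per arm. The Abstract gives 44% in-hospital mortality under standard therapy.
- **Ethical considerations, Consent**: "An estimated >80% of the study population will have altered mental status at initial hospital presentation". It adds that these patients are at the greatest risk of death.

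**The concern.** The outcome is a time to an event that death can prevent. A general linear model on days can use only participants who have a number of days, that is, those who recovered. That group is formed after randomisation, and treatment can change who belongs to it. A rank-sum test avoids this only if deaths and survivors who never normalise are placed at the bad end of the ranking. The sentence on competing risk does not settle the matter, because it is permissive and is attached to two methods that do not use it.

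Faster resolution of coma is a named secondary hypothesis and objective. If the high-dose arms keep alive patients who would have died and who wake slowly, those patients enter the recovered group late and lengthen its average. A real benefit could then be reported as slower recovery, in a trial whose results are meant to guide a phase III choice.

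**Working it through.** **1. The plan's own figure on death.** The GCS endpoint has no stated figure, so the check starts from the survival power statement. Inputs: 20 per arm, one-sided alpha 0.05, hazard ratio 0.285, control survival 0.40 at 8 weeks.

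- Experimental survival = 0.40^0.285 = 0.770.
- Expected deaths = 20 × 0.60 + 20 × 0.230 = 16.6.
- Schoenfeld power = Φ(√16.6 × |ln 0.285| / 2 − 1.645) = Φ(4.074 × 0.628 − 1.645) = Φ(0.91) = 81.9%. With 19 per arm it is 80.2%.

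The stated 80% reproduces. On the plan's own assumptions, 60% of controls and 23% of an experimental arm at that hazard ratio die by week 8. Death is therefore a large competing event and may differ between arms.

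**2. What each named method does with a death.**

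| Method | Participant who dies or never normalises |
|---|---|
| General linear model on days | No outcome value; cannot enter |
| Rank-sum on observed days | Drops out |
| Rank-sum with worst ranks | Enters, but the text states no such rule |
| Cumulative incidence (named for adverse events) | Enters; death is the competing event |

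An ordinary rank-sum test also cannot carry the adjustment for site and BMRC grade that Statistical methods requires of all analyses.

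**3. Direction and size, by illustration.** These assumptions are not in the document: half the patients recover fast (median 4 days) and half slowly (median 20 days); recovery-time distributions are the same in both arms; slow recoverers have 4 times the death hazard; control survival at 8 weeks is 40%. Only participants who normalise by week 8 are compared. The second hazard ratio, 0.42, is the one that the Introduction reports for the earlier Indonesian intravenous study.

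| Hazard ratio for death | Mean days, control v experimental | Median days | Normalise by week 8 |
|---|---|---|---|
| 0.285 | 8.2 v 10.7 | 5.1 v 6.4 | 73% v 85% |
| 0.42 | 8.3 v 10.1 | 5.2 v 6.0 | 73% v 83% |

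At 20 per arm and hazard ratio 0.285, the experimental arm has the longer mean in 74% of simulated trials, against 48% when there is no effect on death. A rank-sum test among recoverers is significant in the wrong direction in about 7%, against 2% with no effect. Giving deaths the worst rank and non-normalising survivors the next worst restores the direction: the probability that an experimental participant does better is 0.535. Cumulative incidence also has the right direction (85% v 73%).

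**4. A cruder check by formula.** Let early recoverers average 5 days and let every rescued patient recover a fixed time later. With death before recovery d_c in controls and d_t in the treated arm, the treated mean among recoverers is 5 + extra × (d_c − d_t)/(1 − d_t).

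- 44% v 25%: 5 + 4 × 0.19/0.75 = 6.0 days; with 7 extra days, 6.8. Control mean 5.0.
- 60% v 23%: 5 + 4 × 0.37/0.77 = 6.9 days; with 7 extra days, 8.4.

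With 16 evaluable per arm (80% of 20), the treated mean is the longer one in 71–82% of trials in the first case and 83–93% in the second, against about 50% by chance. In the first case a rank-sum test among recoverers is significant in the wrong direction in 8–11% of trials. The second case is extreme: it counts every 8-week death as a death before normalisation, and wrong-direction significance would be more frequent there.

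**The case against.** Four stronger readings are tempting, and the document does not support them.

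- *The plan overlooks death.* It does not: it recognises death as a possible competing risk in the sentence after the tests. The fault is that the recognition is optional and does not fit the tests named.
- *Neither method can handle deaths.* That is true of a linear model on days. It is too strong for a rank-sum test, which needs only an ordering and can take deaths as worst ranks.
- *The plan analyses only those who recover.* No sentence says so, and primary analyses are by assigned group. Conditioning on recovery follows if the tests are applied to observed days; it is not a declared population.
- *The trial would probably report the wrong direction.* The percentages in the working come from assumed recovery times. They count any difference in means, against a chance level of about one half. If half of the rescued patients recover at ordinary speed, the 71–82% falls to 61–71%; if treatment also speeds recovery by 25%, it is 53–67%. The hazard ratio 0.285 is a detectable effect in a design that the plan itself calls underpowered for survival, not an expected one. The 44% is in-hospital mortality, and some patients normalise before they die.

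Three further points stand in part. The sentence appears to join two thoughts, and its plural suggests that the tests may serve continuous secondary endpoints in general; the linear model should therefore not be removed for those. A separate analysis plan, not shown, may give rank rules and the handling of survivors who never normalise, so the absence of those details alone is not the point. The consequences are also limited: mortality at 8 and 24 weeks is reported alongside, and the exposure-response analysis uses the proportion who normalise, which does not condition on recovery.

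None of this removes the mismatch in the text: two named tests, a competing event that neither treats as such, and a firmer rule for the same problem in the safety analysis.

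**Conclusion.** The concern holds in a limited form. For time to GCS normalisation, the article names methods that do not, as stated, accommodate death as a competing event, and it leaves competing risk as an option. With the mortality that the plan assumes, an analysis of observed days conditions on recovery. If slow recoverers are likelier to die before normalising, it can make the arm with better survival look slower. In the main illustration the shift is about 2.5 days on the mean and 1.3 days on the median. That size depends wholly on assumed recovery and death hazards, and without a link between slow recovery and death the distortion shrinks.

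The effect is mainly on the point estimate: wrong-direction significance occurred in about 7% of trials in the main illustration and 8–11% in the 44% v 25% case. This is a secondary endpoint; the primary pharmacokinetic and safety conclusions are untouched. The text should be changed before analysis because the change is cheap and the remedy specific.

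**What to change.** For time to GCS normalisation only, replace the permissive sentence with a commitment, in line with the safety analysis. Either of these would do:

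1. Death before normalisation will be a competing event. Arms are compared by the cumulative incidence of normalisation, using Gray's test, or Fine-Gray or cause-specific regression adjusted for site and BMRC grade. Survivors who have not normalised are censored at their last GCS assessment. If cause-specific models are chosen, report those for recovery and for death together with the cumulative incidence curves, because the recovery hazard alone can carry some of the same selection.
2. A rank-based test in which deaths take the worst ranks and non-normalising survivors the next worst, stratified if the adjustment for site and grade is to be kept.

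Do not use a linear model on days for this endpoint. It may stay for other continuous endpoints, and the sentence should be split so that this is clear.

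The cost is wording only; no new data are needed. The result becomes a cumulative-incidence or hazard-ratio contrast, or a rank statistic, rather than a difference in days. Two limits should be accepted. GCS is a separate item in the in-patient schedule but not in the out-patient one, so censoring at the last assessment may be informative after discharge. The change also corrects direction without adding much power: in the main illustration the worst-rank test favoured the experimental arm significantly in only about 5% of trials at 20 per arm.
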